#### Other outcome measures

To assess the expressiveness of personality traits (extraversion, neuroticism, openness to experience, conscientiousness, and agreeableness), the Big Five Inventory (BFI-10) will be used in the pre-treatment assessment [46]. The questionnaire consists of 10 questions, two items per personality trait. Each statement is scored on a 5-point Likert scale (1 = strongly disagree and 5 = strongly agree). The higher the scores on the subscales, the more the personality trait is expressed.

Sociodemographic, tinnitus, and health-related questions will be assessed at pre-treatment. Questions to assess the eligibility for the study and to gather demographic and other important information will be used.

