### Sample size {14}

In order to attain 80% power with a 5% alpha level, a three-means non-inferiority test (ANOVA) was performed, resulting in a required sample size of 42 participants in total. To account for potential dropouts, the number of participants was increased by 25%, resulting in approximately 18 participants per study arm. This dropout rate is common for therapist-guided internet-based interventions. The primary end point used for the non-inferiority test was the THI score at 8 weeks, and the equivalence margin was determined to be 7 points, based on the mean minimally clinically important difference (MCID) found in a prior study [47].

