## Statistical methods

### Statistical methods for primary and secondary outcomes {20a}

The differences between the groups at baseline will be evaluated using independent samples *t*-tests for continuous variables and chi-square tests for categorical variables or their non-parametrical equivalents. In order to assess the potential changes in the primary and secondary outcomes and compare them between the intervention groups and the control group, repeated-measures ANOVAs will be performed. The results from all baseline assessment measures will be utilized as predictors. The study will calculate both within-group and between-group effect sizes. The between-group effect sizes will be determined by calculating the mean difference from the pre-test to the post-test for short-term effects and from the pre-test to follow-up for long-term effects, using the standard deviations of each group at the pre-test. The within-group effect sizes will be calculated using the means and standard deviations at all time points for every group. We will use regression analysis to investigate the association between baseline variables and outcome measures, with the goal of identifying predictors of the outcome.

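### Read in sequence, the analysis section puts every baseline measure (8 instruments, 14 scores) into outcome models with about 14 completers per arm; adjusting for the outcome's own baseline alone is the safer rule

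*Protocol article*

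**What the plan says.** All of the following is in the protocol article.

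- **Outcome models.** Under Statistical methods for primary and secondary outcomes {20a}, to assess change and "compare them between the intervention groups and the control group, repeated-measures ANOVAs will be performed". The next sentence is "The results from all baseline assessment measures will be utilized as predictors".
- **Separate regression.** Later in the same section, after the text on effect sizes: "We will use regression analysis to investigate the association between baseline variables and outcome measures, with the goal of identifying predictors of the outcome".
- **Baseline battery.** Table 1 under Participant timeline {13} lists eight scored instruments at baseline: THI, PHQ-9, GAD-7, ISI, THS, MAAS, TCQ and BFI-10. Secondary outcome measures gives THS three subscales. For BFI-10, Other outcome measures says "The questionnaire consists of 10 questions, two items per personality trait", over five traits. An unstated number of sociodemographic, tinnitus and health questions comes on top.
- **Sample.** Sample size {14} describes a three-means ANOVA calculation "resulting in a required sample size of 42 participants in total", then a 25% increase "resulting in approximately 18 participants per study arm". It mentions no covariates.
- **Analysis set.** Section {20c} calculates results per protocol and compares them with intention to treat, using multiple imputation if necessary.

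**The concern.** Each covariate costs an error degree of freedom and adds some random variation to the adjusted arm contrast. That cost is repaid only if the covariate explains enough outcome variance. Baseline THI is the natural candidate for week-8 THI. Personality traits, hearing scores, mindfulness and the rest may add little once THI is in the model, and the protocol gives no reason to expect otherwise.

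With 14 people per arm there is little room for covariates that do not pay their way. The trial judges non-inferiority at 8 weeks against a 7-point THI margin, so interval width bears directly on whether it can reach a conclusion. The number of terms is also not fixed: all baseline measures can mean 8 totals, 14 scores, or more once demographic items are included.

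**Working it through.** **Plan's own figures.** The required 42 cannot be reproduced, because no standard deviation is stated. The inflation can: 42 × 1.25 = 52.5, or 17.5 per arm, rounded to 18 (54 in total). Losing 25% of 54 leaves 40.5, so about 42 completers is a fair figure for the per-protocol set.

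**Covariate count.** THI, PHQ-9, GAD-7, ISI, MAAS and TCQ give 6 totals, THS gives 3 subscales and BFI-10 gives 5 traits: 6 + 3 + 5 = 14. If each instrument counts once, the number is 8. Demographic and health items are in neither count.

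**Formula.** Let N be the people analysed, g = 3 arms, p the number of covariates and R² the share of outcome variance they explain jointly. The expected variance of an arm contrast, relative to no covariates, is

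(1 − R²) × (N − g − 1) / (N − g − p − 1), with error df = N − g − p.

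**Three-arm model, N = 42.**

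- Error df: 39 with no covariates, 38 with THI alone, 25 with 14.
- THI alone, cost before any gain: 38/37 = 1.027, SE × 1.013.
- 14 covariates against none, if they explain nothing: 38/24 = 1.583, SE × 1.26.
- 14 covariates against THI alone, if the other 13 add nothing: 37/24 = 1.542, SE × 1.24. With the larger t quantile at 25 df, the 95% interval is × 1.26.
- Break-even for the other 13: they must explain 1 − 24/37 = 35% of the variance left after THI to recover the SE, and about 37% to recover the interval width.

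**Milder readings, covariates explaining nothing beyond THI (last column) or nothing at all (middle column).**

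| Case | SE against no covariates | SE against THI alone |
|---|---|---|
| N = 42, 14 scores | √(38/24) = 1.26 | √(37/24) = 1.24 |
| N = 42, 8 totals | √(38/30) = 1.13 | √(37/30) = 1.11 |
| N = 54, 14 scores | √(50/36) = 1.18 | √(49/36) = 1.17 |

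The N = 54 row takes imputed records at face value. Its break-even share against THI alone is 27–28%.

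**Net effect against other comparators** (N = 42, 14 scores; the baseline-to-week-8 THI correlation is assumed, since none is stated).

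- Against an unadjusted week-8 comparison, with only THI predictive, interval width is × 1.17 at a correlation of 0.4, × 1.11 at 0.5, × 1.02 at 0.6, × 0.91 at 0.7 and × 0.77 at 0.8.
- Against the change-score contrast of a two-point repeated-measures ANOVA, over correlations 0.4–0.8, it is × 1.07 to 1.22 if the other 13 add nothing. It is × 0.96 to 1.09 if they explain 20% of the remaining variance, and × 0.86 to 0.98 if they explain 35%.

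**Simulation** (1,500 runs per scenario, N = 42). At a correlation of 0.5 with nothing from the other 13, the mean widths of the 14-covariate and THI-only intervals stand at 1.67/1.33 = 1.26. When the 13 explain 35% of the remainder, the ratio is 1.354/1.333 = 1.02. Both agree with the formula.

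**The case against.** The best counter-argument is that the sentence may not concern the ANOVAs. It speaks of predictors, a word the section uses again for the separate regression. Outcomes {12} also says personality and sociodemographic variables are collected to study personal factors linked to efficacy. This reading is possible. However, the sentence directly follows the ANOVA sentence and comes before the effect-size text, while the regression arrives later with its own stated aim. On the alternative reading the sentence would be redundant. The covariate reading is the more natural one, though not certain.

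It can also be said that an article leaves covariate lists to the full plan. That would answer a complaint about missing detail. Here a rule is stated, and it is a poor one.

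A reader might infer more than the documents support:

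- **That the contrasts must widen.** This depends on how much variance the covariates explain, which the protocol does not give, and on the comparator. At an assumed correlation of 0.7 or more, even the 14-covariate model beats an unadjusted week-8 comparison, although THI alone would secure that gain more cheaply.
- **That the penalty is larger because only the two active arms count.** The protocol describes three-group analyses and no covariate-adjusted fit restricted to the active arms.
- **That collinearity among the distress scales destabilises the treatment effect.** It destabilises the covariates' own coefficients. The arm contrast depends on the space the covariates span, and the formula has no collinearity term.
- **That using baseline THI both as first repeated level and as covariate biases the result.** With pre and post only, the baseline-adjusted time-by-group contrast equals the ANCOVA contrast recommended below.

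**Conclusion.** The point holds as a badly fixed covariate rule. On the natural reading, the outcome models carry 8 to 14 baseline terms, plus demographic items, on about 14 completers per arm. With 14 scores and 42 people, the cost against THI-only adjustment is about 24% in SE and 26% in interval width, unless the other 13 scores explain roughly 35–37% of the variance left after THI. With 8 totals or the 54-person set it is smaller.

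The conclusion rests on three things: that the sentence governs the ANOVAs, that the subscales are entered separately, and that the additional scores add little. The last is an assumption, because the protocol gives no correlation or R². The documents support a material and avoidable risk to precision. They do not support a claim that the intervals will certainly be wider.

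**What to change.** Replace the sentence with one that names the model and the covariate. Each outcome model adjusts only for the baseline value of that outcome (baseline THI for the primary), entered as a covariate, with assessments from week 8 onwards as the outcome. All other baseline measures enter only the predictor regression already described in {20a}, labelled exploratory. If the sentence was meant for that regression all along, the same edit settles the ambiguity.

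The cost is one sentence, plus the ethics approval and register entry that the protocol requires for any change. Data collection and recruitment are unaffected. The statistical downside is giving up any precision the other baseline scores would have brought, which becomes a net loss only if they exceed the break-even share above.

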### Interim analyses {21b}

No interim analyses are planned.

### Methods for additional analyses (e.g., subgroup analyses) {20b}

Subgroup analyses are not planned.

### Methods in analysis to handle protocol non-adherence and any statistical methods to handle missing data {20c}

The results will be calculated based on the per-protocol approach and will also be compared with those obtained using the intention-to-treat approach. To perform the intention-to-treat analysis, a missing value analysis will be carried out. If necessary, missing data will be filled in using multiple imputation techniques.

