### Objectives {7}

The purpose of this study is to assess the efficacy of Internet-delivered cognitive behavioral therapy (CBT) and Internet-delivered mindfulness-based tinnitus stress reduction intervention for adults with tinnitus, by comparing their efficacy against each other and against a waiting list control group.

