### Trial design {8}

This study is three-armed parallel-group randomized controlled non-inferiority trial. Participants will be randomized to all groups equally.

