##### Internet-delivered cognitive behavioral therapy for tinnitus (ICBT)

The ICBT intervention for the experimental group will start after group allocation. The ICBT is based on a self-help program created by Andersson and colleagues and is designed to address the physical, emotional, and problematic effects of tinnitus for habituation [35]. The program includes key audiological principles and has been modified previously to an interactive e-learning format for better engagement [10]. The 16 recommended modules and 5 optional modules can be tailored to individual needs and are released weekly over an 8-week period. Participants are encouraged to engage with the modules and practice the suggested techniques daily. The program is comprehensive, offering a range of CBT techniques, and can be accessed online, downloaded, or printed. It includes information, videos, quizzes, diagrams, worksheets, and solutions for common problems. Participants can also use a secure messaging system to ask questions and receive feedback from their assigned program therapists.

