##### Internet-delivered mindfulness-based tinnitus stress reduction.

The i-MBTSR course consists of 8 online lessons held weekly, which include videos, audio recordings, and written content covering tinnitus education, mindfulness, gentle yoga, and guided meditations [25]. Participants are required to do 30 min of daily meditation and attend a daylong practice session between the 6th and 7th week to enhance their mindfulness skills. The course aims to provide in-depth tinnitus education, reduce tinnitus-related anxiety, and teach meditation skills to help participants view tinnitus as a normal part of their sensory experience, reducing its bothersome effects. Just like the ICBT participants, individuals assigned to iMBTSR group will also have the ability to use the same secure messaging system to ask questions and receive feedback from their assigned program therapists.

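### Per-protocol leads every comparison, including those with the waiting list, where intention-to-treat should be primary

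*Protocol article*

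**What the plan says.** Section {20c} of the protocol article, on non-adherence and missing data, fixes the analysis sets in one sentence: "The results will be calculated based on the per-protocol approach and will also be compared with those obtained using the intention-to-treat approach". Imputation belongs to the intention-to-treat analysis and is conditional: "If necessary, missing data will be filled in using multiple imputation techniques".

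The sentence covers all results, but the trial asks two kinds of question. Trial design {8} labels it as non-inferiority: "This study is three-armed parallel-group randomized controlled non-inferiority trial. Participants will be randomized to all groups equally". Objectives {7} sets out to assess both programmes "by comparing their efficacy against each other and against a waiting list control group", and Statistical methods {20a} plans the waiting-list comparison explicitly: to "compare them between the intervention groups and the control group, repeated-measures ANOVAs will be performed".

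The arms differ in what there is to adhere to. Under Intervention description {11a}, the control group waits 8 weeks and then chooses a programme. ICBT offers modules over the same period ("The 16 recommended modules and 5 optional modules can be tailored to individual needs and are released weekly over an 8-week period"), and iMBTSR has 8 weekly lessons plus home practice.

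**The concern.** Per-protocol produces the results and intention-to-treat is what they are checked against. For a comparison with a waiting list, that order is the wrong way round. Someone who waits cannot fail to complete a programme, so a filter on programme adherence removes people mainly from the active arms. Those who remain are a self-selected part of a randomised group, set against a nearly complete control group. If people who persist also tend to improve more for reasons unrelated to treatment, the comparison shows a benefit even where there is none.

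The usual argument for per-protocol, that it guards against a false claim of non-inferiority, does not carry over to superiority over no treatment. Arms are small (about 18 each, Sample size {14}), so a few exclusions matter. Who will be blinded {17a} adds that analysts will be able to identify the groups.

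**Working it through.** **The plan's own figures.** Sample size {14} gives 42 participants, raised by 25% to about 18 per arm. 42 × 1.25 = 52.5, and 52.5 / 3 = 17.5, which rounds to 18. The base of 42 cannot be rebuilt because no SD is stated, but that does not bear on this point. Only the arm size of 18 is used below.

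**Assumed inputs (not in the document).**
- q: share of an active arm kept in the per-protocol set, 0.50 to 0.90.
- ρ: correlation between the tendency to adhere and THI improvement unrelated to treatment, 0.2 to 0.5.
- SD of THI change: 10 to 20.
- No true treatment effect, and the whole waiting list kept.

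**Expected spurious benefit.** If adherence follows a normal propensity cut so that a share q is kept, the mean of the retained group shifts by

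bias = ρ × SD × φ(c) / q, with c = Φ⁻¹(1 − q).

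For q = 0.75: c = −0.674, φ(c) = 0.318, φ(c)/q = 0.424. With ρ = 0.3 and SD = 15, bias = 0.3 × 15 × 0.424 = 1.9 THI points.

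**False-positive rate.** This was simulated with 18 per arm randomised, 8,000 trials per setting, SD 15 and a two-sided 5% t-test. Rejections favouring the active arm were counted (nominal 0.025).

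| Retained in active arm | ρ | Spurious benefit (THI points, formula) | False-positive rate |
|---|---|---|---|
| 100% (as randomised) | 0.3 | 0 | 0.024 |
| 75% | 0.3 | 1.9 | 0.052 |
| 75% | 0.5 | 3.2 | 0.085 |
| 60% | 0.3 | 2.9 | 0.068 |
| 60% | 0.5 | 4.8 | 0.123 |
| 50% | 0.3 | 3.6 | 0.080 |
| 50% | 0.5 | 6.0 | 0.153 |

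Over the whole assumed grid the bias runs from 0.4 points (q = 0.90, ρ = 0.2, SD = 10) to 8.0 points (q = 0.50, ρ = 0.5, SD = 20).

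**Between the active arms.** The same formula gives the shift when retention differs: ρ × SD × [φ(c₂)/q₂ − φ(c₁)/q₁]. For 75% versus 60% retained, with ρ = 0.2 and SD = 10, it is 0.2 × 10 × (0.644 − 0.424) = 0.4 points. For 90% versus 50%, with ρ = 0.5 and SD = 20, it is 0.5 × 20 × (0.798 − 0.195) = 6.0 points. The shift favours whichever arm keeps fewer people, against a margin of 7 points. This shows what unequal retention would do. It does not show that retention will be unequal, or in which direction.

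**The case against.** Section {20c} never calls per-protocol primary, and it commits to both analyses. The trial is framed and sized as non-inferiority, where per-protocol beside intention-to-treat is customary. Discontinuing participants will still be asked for questionnaires (section {18b}). All of this stands: intention-to-treat is not missing, and the defect is which analysis leads. The definition of the per-protocol set and a rule for disagreement may sit in an analysis plan that is not shown, so their absence is not counted.

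Three stronger readings are tempting, and the document does not support them.

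- **A filter stricter for iMBTSR, pushing towards non-inferiority.** A reader might infer this from iMBTSR's wording ("Participants are required to do 30 min of daily meditation and attend a daylong practice session between the 6th and 7th week") set against ICBT's ("Participants are encouraged to engage with the modules and practice the suggested techniques daily"). These sentences describe the programmes, and nothing makes them per-protocol criteria. On content counts, ICBT's 16 recommended modules against iMBTSR's 8 lessons could make a completion filter stricter for ICBT. The direction is open.
- **Exclusions from the active arms only.** Waiting-list members can also breach the protocol, since other tinnitus interventions during the study are an exclusion criterion ({10}) and other psychological interventions may not be started ({11d}). They can also miss the week-8 questionnaire. The supportable statement is that exclusions fall mainly on the active arms.
- **An effect inflated by 1.33.** This comes from 1 / (1 − 0.25), which treats the 25% in {14} as active-arm non-adherence with no benefit. The 25% is a dropout allowance for all arms, and adding it to 42 covers a loss of 10.5 / 52.5 = 20%, which would give 1 / 0.80 = 1.25. Zero benefit for partial users also sits badly with the protocol's background section, which reports that the earlier online iMBTSR study saw its largest gains by mid-treatment.

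**Conclusion.** The point holds for the comparisons with the waiting list. As written, section {20c} rests them on a selected subset, with an expected bias in favour of the interventions if adherers improve more regardless of treatment. The size is an illustration: about 1.9 THI points and a one-sided false-positive rate of about 0.05 instead of 0.025 at 75% retention, ρ = 0.3, SD 15 and a complete waiting list. The document gives no adherence rate, correlation or SD, and exclusions from the waiting list would change these figures.

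For ICBT versus iMBTSR the conclusion is narrower. Per-protocol is a proper companion analysis, but exclusions may differ between the arms in a direction the document does not settle. It should therefore not stand alone, nor be presumed conservative.

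**What to change.** In section {20c}:

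1. Make intention-to-treat (all randomised participants, as allocated, using the multiple imputation already planned) the primary analysis for ICBT versus waiting list and for iMBTSR versus waiting list, with per-protocol as a sensitivity analysis.
2. For ICBT versus iMBTSR, conclude non-inferiority only if the intention-to-treat interval and the per-protocol interval both exclude a 7-point loss.

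This changes wording, not data collection, because questionnaires from those who discontinue are already to be sought. The price is that estimates against the waiting list may be smaller and the non-inferiority claim slightly harder to reach.

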#### Primary outcome measures

To assess the impact of tinnitus on daily life, the Tinnitus Handicap Inventory (THI) will be used [37]. Assessment with THI will take place at pre-treatment, post-treatment at week 8, and 3 and 12 months post-treatment follow-ups. Change in the score from baseline will be assessed. The THI is designed to assess the impact of tinnitus on daily life and measures tinnitus-related functional limitations and emotional and catastrophic reactions. It is also widely used in research studies to measure the change in the severity of a tinnitus handicap before and after an intervention and therefore was selected as the primary measure of the study. The THI questionnaire consists of 25 questions. Answers are scored as follows: “yes,” 4 points; “no,” 0 points; and “sometimes,” 2 points. The total score is obtained by summing the scores of all 25 questions. A higher score indicates a higher disability caused by tinnitus and a higher impact of tinnitus on a person’s daily life. A validated Lithuanian language version of THI will be used in the study [38].

Weekly monitoring of changes in tinnitus handicap severity will be done using the Tinnitus Handicap Inventory Screening version (THI-S) [39]. A screening version of THI has 10 items from the original THI and will let assess the changes throughout the duration of the program. Assessment with THI-S will be done at weeks 2, 4, and 6.

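### The ITT analysis imputes only at an undefined discretion, so a completer result can be reported as ITT beside the per-protocol result

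*Protocol article*

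**What the plan says.** Section {20c} of the protocol article names the per-protocol approach first and compares it with ITT. For ITT it says: "To perform the intention-to-treat analysis, a missing value analysis will be carried out". The next sentence is: "If necessary, missing data will be filled in using multiple imputation techniques". It gives no criterion for necessity and no ITT method for the case where imputation is not done.

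Section {20a} analyses the primary and secondary outcomes by repeated-measures ANOVA. Section {17a} says that data analysts will not be blinded.

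Section {14} makes week-8 THI the endpoint of the non-inferiority test, with this margin: "the equivalence margin was determined to be 7 points". On dropout it says: "the number of participants was increased by 25%, resulting in approximately 18 participants per study arm".

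Under Primary outcome measures, a 10-item screening version of the THI is also collected: "Assessment with THI-S will be done at weeks 2, 4, and 6". Neither {20a} nor {20c} mentions it by name.

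**The concern.** Whether the ITT analysis covers everyone randomised depends on a judgement made after the data are seen, by people who can see the arms, under a condition that is not defined. If the judgement is that imputation is not needed, the only stated method left is an ANOVA that needs complete data. The analysis labelled ITT then covers completers.

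This matters more in a non-inferiority trial. The comparison of per-protocol with ITT is meant to show whether the conclusion depends on who was kept. If both sets exclude those without a week-8 score, they share the same selection, and their agreement says nothing about it.

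If participants who are doing badly leave one programme more than the other, the contrast between programmes moves in favour of that programme. If they leave a programme but not the waiting list, the benefit over waiting is overstated.

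**Working it through.** **Expected missing data.** Section {14} starts from 42 participants. 42 × 1.25 = 52.5, or 17.5 per arm, which reproduces the stated 18 per arm (54 in total). At 25% dropout, 54 × 0.25 = 13.5, so about 14 would be missing and 40 observed. Section {18a} forces complete answers, so the gaps will be whole questionnaires, not single items.

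**What happens without imputation.** A standard repeated-measures ANOVA keeps only participants with every time point in the model. Those without a week-8 score drop out, which leaves about 40 of 54.

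**What a missing value analysis could show.** It can compare only observed variables, so it cannot see the missing week-8 values. The document names no test. Suppose, as an assumption, that it is a two-sided 5% t-test of 14 dropouts against 40 completers on an observed variable. The noncentrality is d × √(14 × 40 / 54) = 3.22 d, with 52 degrees of freedom:

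| True difference | Noncentrality | Power |
|---|---|---|
| 0.3 SD | 0.97 | 16% |
| 0.5 SD | 1.61 | 35% |
| 0.8 SD | 2.58 | 72% |

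A difference of about 0.9 SD is needed for 80% power. In the two programmes alone (9 against 27), power at 0.5 SD is 24%. A null result would say little.

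**Size of a possible bias.** In one arm, the completer mean differs from the mean of all randomised by dropout share × (completer mean − dropout mean). At 25%, a shift of 1 point needs a gap of 1 / 0.25 = 4 THI points, and a shift of 3 points needs a gap of 12.

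A simulation gives a scale for this. It assumes 18 per arm and about 25% dropout, with dropout in one arm more likely as an interim score worsens and dropout in the other arm at random. It uses 6,000 replicates per setting. With an interim-to-week-8 correlation of 0.5 to 0.7, the completer contrast is biased by 0.117 to 0.150 SD.

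The document gives no SD, so a range is needed. The lower end comes from solving for 14 per arm with margin 7, true difference 0, one-sided 5% and 80% power: SD = 7 / [(1.645 + 0.842) × √(2/14)] ≈ 7.4. The values 15 and 20 are assumptions.

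| SD | Bias, THI points | Share of the 7-point margin |
|---|---|---|
| 7.4 | 0.9 to 1.1 | 12% to 16% |
| 15 | 1.8 to 2.3 | 25% to 32% |
| 20 | 2.3 to 3.0 | 33% to 43% |

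With the same selective mechanism in both arms, the bias of the contrast is about zero.

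**What the interim score recovers.** In that simulation, regression on the interim score reduces the bias to between 0.00 and −0.01 SD. This is a best case, because dropout depends on exactly that score and every dropout supplies it. A second simulation assumes that half the dropouts leave before week 6 with only a week-2 score. There, about 42% to 47% of the bias remains (for example 1.09 of 2.33 points at SD 20).

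**The case against.** The strongest reply is that *if necessary* may simply mean *if values are missing*. At the dropout allowed for, imputation would then be done. The document names no significance test, threshold or comparison of dropouts with completers, so a reader who infers that a weak test decides on imputation goes beyond the text. This stands: the power figures illustrate one possible reading, and it cannot be said that imputation would usually be skipped. It does not rescue the wording. On the benign reading the condition adds nothing; on the other it opens the choice described above.

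A reader might also infer that imputation would use baseline data only, or that THI-S is left out of every analysis. The document supports neither. THI-S stands under Primary outcome measures, and {20a} covers the primary outcomes. The variables in an imputation model are commonly left to the statistical analysis plan. Their absence is not an error here; using THI-S is a recommendation.

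Section {18b} provides for participants who discontinue or deviate to be contacted and asked for questionnaires. Leaving a programme is therefore not the same as a missing outcome, and the loss may be smaller than 25%. That reduces the problem but does not remove it.

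Finally, nothing in the document says that poor responders leave or that one programme loses more of them. The daily practice and daylong session in the mindfulness arm make differential loss conceivable, but they are not evidence of it.

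**Conclusion.** The point holds as a defect of rule: {20c} permits a completer analysis to be reported as ITT, at the discretion of unblinded analysts, with about a quarter of participants allowed for as dropouts. That conclusion rests on the document's text and on the standard behaviour of repeated-measures ANOVA.

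The consequence is conditional. About 1 to 3 THI points, or 12% to 43% of the margin, applies if dropout is selective in one arm only, at 25%, with the SDs and correlations assumed above. If selection is alike in both programmes, the contrast between them is about unbiased. The document does not support the stronger conclusion that the non-inferiority result will be biased, or biased in a known direction.

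**What to change.** In {20c}, delete *if necessary* and state that the ITT analysis of week-8 THI includes all randomised participants, whatever the missing value analysis shows. The missing value analysis can stay as a description.

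Name the method: multiple imputation, or a likelihood-based mixed model, using arm, baseline THI and the THI-S scores already collected. With 18 per arm the model must stay short, for example baseline THI plus the last available THI-S. THI-S is not on the full THI scale, so in a mixed model it should enter as a second outcome, not as an extra THI visit. Confirm that THI-S is also collected in the waiting-list arm, since its stated purpose is to follow change during the programme.

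This reduces bias but does not guarantee its removal, especially for those who leave early. A sensitivity analysis that worsens the imputed values in one programme by fixed steps up to 7 points would show when the conclusion changes; it is optional.

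The cost is a change of wording, slightly more analysis work and possibly slightly wider intervals. No new data, visits or participants are needed.
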